### Aims

The main objective of this project is to assess the risk of malnutrition and nutritional status on admission and its evolution until discharge, in patients aged 65 and over admitted to medical and surgical units in hospitals of the Spanish National Health System. In addition, the aim is to respond to the following specific objectives:

To identify the incidence and prevalence of risk of malnutrition and the presence of malnutrition and associated factors on patient admission and discharge.To describe the evolution of nutritional status during patient hospitalization.To analyze the average length of stay, hospital mortality, and early readmission as a function of nutritional status at admission and the presence of dysphagia in the study cohort.To determine the incidence and prevalence of dysphagia and associated factors on admission and discharge.To determine satisfaction with the quality of patient nutrition at discharge, the type of hospital food service, and the characteristics of the hospital nutrition unit.

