### Variables and instruments

The study variables are organized into eight groups: i) Nutritional status; ii) Dysphagia; iii) Food quality and environment; iv) Socio-demographic variables; v) Clinical, functional, cognitive, and frailty variables; vi) Variables related to the risk profile; vii) Context variables; viii) Variables related to the care process.

Specifically, nutritional status and dysphagia are considered the main variables of the study. Likewise, the variables related to nutritional status are organized into:

Risk of malnutrition on admission: Malnutrition Universal Screening Tool (MUST) will be used to determine the risk of malnutrition. This questionnaire will measure current weight (kg), estimated weight three months ago (kg), height (cm), and Body Mass Index (BMI) (kg/m2). If height and weight cannot be measured or obtained, they will be estimated mid-upper arm circumference (MUAC) and calf circumference (CC) are set for weight and forearm length for height by the nutrition staff of each hospital. All patients included in the study will be assessed on admission, every 7 days, and at discharge.Diagnosis of malnutrition and degree of severity at admission: Global Leadership Initiative on Malnutrition (GLIM) criteria will be used for the population identified as high risk according to MUST. In addition, the following biochemical parameters will be collected: albumin, prealbumin CRP, CRP/prealbumin ratio, transferrin, total cholesterol, and the total number of lymphocytes. They will be collected on admission, every 7 days, and discharge provided that the minimum time for their re-determination has elapsed.Type of nutritional care established (according to risk and diagnosis of malnutrition): Includes aspects such as referral to the nutrition and dietetics unit, dietary adaptation according to alteration, nutritional supplementation, type of nutrition, or nutritional education. It will be recorded within 48 hours of admission, every 7 days and at discharge, and in case of any modification in the selected intervention, the starting date should be noted.Daily intake: a semi-quantitative questionnaire will be used to record the amount of intake made during the days of admission.

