#### Phase 2: Follow-up

Participants will be monitored every 7 days until they are discharged from the hospital. In this way, the researchers in charge will make a forecast of follow-up dates. In addition to the variables indicated, the nutritional care established will be adapted according to the evolution of the nutritional status and degree of dysphagia of the patient during their hospital stay, as part of the usual practice in each centre. On each occasion, a record will be kept of the person collecting the data.

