#### Phase 3: Situation on discharge

In addition to the variables indicated, on the day of discharge from the hospital, the daily intake record book will be collected and the food satisfaction survey will be provided. The variables related to the care process (days of stay, hospital mortality, and whether it was early readmission) will also be recorded.

Finally, the patient will be given the continuity of care report at discharge, drawn up by the responsible physician together with the nursing recommendations and information sheets on care related to malnutrition or dysphagia, as appropriate.

Data collection will be carried out electronically through Research Electronic Data Capture (REDCap) (www.prooject-redcap.org) [25,26]. This is a web application that allows the creation of electronic data notebooks for research projects and their online and offline collection from computers and other mobile devices. It also includes a scheduling and alarm system to manage data collection during monitoring. In this regard, it should be noted that the researchers who take on the data collection will receive training on the operation of REDCap and that a pilot of the process of recruiting participants and data collection will be carried out for one month.

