### Data analysis

A descriptive analysis of all the study variables will be carried out, using the appropriate measures according to the type of variable and their corresponding 95% CIs. Firstly, depending on the groups to be compared and compliance with the application requirements, a bivariate analysis will be performed, including the chi-squared or Fisher’s exact test (qualitative variables) and Student’s t-test, ANOVA, Mann-Whitney U-test, or Kruskal-Wallis (quantitative variables), depending on the application conditions.

For the analysis of the evolution of the risk of malnutrition, McNemar’s test or Cochran’s Q test will be used for qualitative variables and paired t-test or Friedman’s rank test for quantitative variables. The incidence of risk of malnutrition and undernutrition will be calculated, as for dysphagia, during the care process and at patient discharge, estimating their corresponding Odds Ratios and 95% CI using logistic regression models.

To assess the possible risk factors for both malnutrition and dysphagia and the socio-demographic and clinical characteristics of the patients, multivariate logistic regression models will be constructed. As independent variables will include: type of nutritional care established according to the risk of malnutrition; daily intake; suspected and diagnosed dysphagia and days of stay. As control variables will include: those related to the risk profile; sociodemographic (sex, age); clinical, functional, cognitive and frailty variables. In the case of mortality and time to readmission, multivariate Cox regression models will be fitted. Independent variables will be included: level of risk of malnutrition at admission; diagnosis of malnutrition at admission; change in risk of malnutrition at admission, at 7 days and at discharge; change in nutritional status at admission, at 7 days and at discharge. Control variables will include: type of nutritional care established (according to risk of malnutrition); daily intake; contextual; related to risk profile; sociodemographic; clinical, functional, cognitive and frailty variables; suspected and diagnosed dysphagia. In all multivariate models, possible interaction effects and possible collinearity will be analyzed.

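### Change in nutritional risk and status at discharge cannot be a predictor in the Cox model for hospital mortality, because patients who die in hospital have no live-discharge value

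*Protocol article*

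**What the plan says.** The Data analysis section of the article states: "In the case of mortality and time to readmission, multivariate Cox regression models will be fitted". One list of independent variables then follows for both outcomes. It holds the risk level and the malnutrition diagnosis at admission, then "change in risk of malnutrition at admission, at 7 days and at discharge" and "change in nutritional status at admission, at 7 days and at discharge". No term is assigned to only one of the two outcomes.

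The word mortality is unqualified there, but elsewhere it means death in hospital. The third specific objective under Aims concerns "hospital mortality, and early readmission as a function of nutritional status at admission and the presence of dysphagia", and the Research hypothesis and the Conclusions also speak of hospital mortality. Phase 3 says: "The variables related to the care process (days of stay, hospital mortality, and whether it was early readmission) will also be recorded". Phase 2 says: "Participants will be monitored every 7 days until they are discharged from the hospital". The article describes no follow-up of deaths after discharge.

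On the timing of nutritional measurements, Variables and instruments says: "All patients included in the study will be assessed on admission, every 7 days, and at discharge". The only missing-data rule, at the end of Data analysis, is multiple imputation for losses to follow-up. Patients who die are not mentioned.

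**The concern.** A Cox model compares, at each death, the patient who dies with those still at risk, using what is known at that moment. A change measured at discharge is not known then. For the patient who dies it never exists. For the comparators it lies in the future and reflects the rest of a stay that they had to survive. The longer a patient stays alive in hospital, the more time there is to be seen to worsen, so worsening becomes a marker of survival.

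The Research hypothesis holds that nutritional status evolves unfavourably and that this may raise hospital mortality. The discharge terms are the ones that would test that link over the whole stay, and they are biased against it. A real harm could be masked or appear as a benefit.

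**Working it through.** **The plan's own figures.** No event count, hazard ratio or power is stated for the Cox models. The sample size rests on precision for a prevalence: 1.96² × 0.5 × 0.5 / 0.05² = 384.15, rounded up to 385; 385 / 0.85 = 452.9, so 453 per hospital; 9 × 453 = 4077. This reproduces the article, and 4077 is the cohort size used below.

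**Step 1, no assumptions needed.** Every in-hospital death lacks a live-discharge assessment. A complete-case fit that includes a discharge-change term therefore contains no deaths and cannot be estimated.

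**Step 2, why a fixed covariate reverses the sign.** Take a mean stay of 10 days, 5% mortality, discharge no earlier than day 2 (echoing the 48-hour entry criterion), and worsening at 0.18 / 8 = 0.0225 per day. The 18% is the in-hospital figure quoted in the Introduction; the 8 days and the other rates are assumptions. Let worsening have no effect on death.

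- The discharge hazard is 0.95 / 10 = 0.095 per day, a mean of 10.53 days. Less the 2-day floor, a patient still in hospital after day 2 has on average 8.53 days to go.
- A patient who dies on day 5 has worsened with probability 1 − exp(−0.0225 × 5) = 0.106 (odds 0.119).
- A comparator in hospital on day 5 has worsened by discharge with probability 1 − exp(−0.1125) / (1 + 0.0225 × 8.53) = 1 − 0.894 × 0.839 = 0.250 (odds 0.334). Deaths among comparators are ignored.
- Apparent hazard ratio at that death: 0.119 / 0.334 = 0.36.
- The same sum for a death on day 20 gives 0.362 (odds 0.568) against 0.465 (odds 0.869), a ratio of 0.65.

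Every such comparison falls below 1 although the truth is 1.

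**Step 3, simulation.** 4077 patients, 20 replicates per scenario, mean stay 7, 10 or 14 days, hospital mortality about 5% or 10%, worsening 0.0225 per day, true hazard ratio 1.0 or 2.0. Average deaths per scenario were about 200 to 490. Ranges are of mean hazard ratios across the six stay-by-mortality combinations.

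| Handling | Truth 1.0 | Truth 2.0 |
|---|---|---|
| Discharge change, complete case | no deaths left | no deaths left |
| Discharge change, deaths take last scheduled 7-day value | 0.20–0.28 | 0.36–0.48 |
| Discharge change, deaths imputed from survivors (overall, or within fifths of stay) | 0.43–0.67 | 0.47–0.66 |
| Status at death known exactly, entered as fixed | 0.41–0.48 | 0.77–0.90 |
| 7-day change, landmark at day 7 | 0.99–1.08 | 1.57–2.04 |
| Worsening as a time-dependent covariate | 0.96–1.07 | 1.91–2.07 |

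A landmark fixes status at day 7, so patients who worsen later sit in the reference group and a true effect is diluted. The time-dependent fit used the exact time of worsening; with assessments only every 7 days some dilution should be expected there too.

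**Step 4, a different shape of stay.** With 3,465 patients (4077 × 0.85), a lognormal stay (median 7 days, log-SD 0.7), death at 0.6% per day, worsening at 3% per day and no true effect, 60 cohorts gave a mean hazard ratio of 0.22 for worsening at the last assessment including discharge, and 0.99 for the day-7 landmark.

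**Step 5, the 7-day term.** It is missing for anyone who dies or leaves before day 7: 38–73% of deaths across the Step 3 scenarios and 61% in Step 4. Patients who die later do have it. A complete-case fit of this term alone gave the same estimates as the landmark, so early deaths are lost but the hazard ratio is not reversed.

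**The case against.** **The article is condensed and shares one list between two outcomes.** Discharge change is a proper predictor of readmission, and a fuller plan may split the list or specify time-dependent coding. This stands for the 7-day values: three listed time points are compatible with such coding, and silence on it is not an error. It does not rescue the discharge terms, because no coding supplies a live-discharge value for a patient who died in hospital.

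**Mortality might include deaths after discharge.** With a clock starting at live discharge the term would be legitimate. But the article names only hospital mortality and describes no later follow-up of deaths.

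**Multiple imputation is planned.** It is worded for losses to follow-up, and death is the outcome. If it were applied to deaths, no death has an observed discharge value, so the data carry no information on the association being estimated. Imputing from survivors still gave 0.43–0.67 under no effect.

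**Stronger readings that the article does not support.**

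- A reader might infer that the 7-day term also reverses the hazard ratio. In the Step 4 setting it does (0.45), but only if patients not assessed are coded as unchanged, a rule found nowhere in the article.
- The reference to change at admission looks like loose wording for change across the three time points, and is not a separate defect.
- One might say that the admission hazard ratio is distorted by adjusting for later change. That would follow only if both sets of terms enter one model, which the article does not say outright.

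**Importance.** The link between change and mortality is not the main objective, and the third specific objective asks about status at admission, for which suitable predictors are already listed. This stands and limits the reach of the problem.

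**Conclusion.** The point holds for the discharge-change terms in the hospital-mortality model. That these terms are missing for every death follows from the article's own definitions and depends on no assumed rate. The size of the bias under other handlings does depend on assumed stay, mortality and worsening rates: with no true effect, mean hazard ratios of about 0.2–0.3 (last value carried forward), 0.4–0.7 (imputation from survivors) and 0.4–0.5 (status at death known). A true doubling of hazard also came out below 1 in each of these. A stronger true effect with status recorded up to death could exceed 1, though still biased downward.

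The 7-day change is a lesser matter: absent for roughly 40–70% of deaths under these assumptions, and valid only in a landmark or time-dependent analysis. The readmission model is unaffected if its clock starts at live discharge, and the main objective does not depend on this model.

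**What to change.** Give the two Cox models separate predictor lists.

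- **Hospital mortality, third specific objective:** admission variables only, with every discharge-change term removed.
- **Evolution and hospital mortality:** a separate model, either a day-7 landmark (patients alive and in hospital at day 7, deaths counted from then) or the scheduled 7-day assessments as time-dependent covariates.
- **Both mortality models:** treat live discharge as a competing event, because leaving hospital alive ends the possibility of hospital death and is related to prognosis.
- **Readmission:** start the clock at live discharge and keep change up to discharge here only. Use the 7-day change only in patients whose stay reached day 7.

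No new nutritional measurements are needed. The cost is rewording the Cox paragraph and one extra model. A landmark model uses fewer deaths, so its interval will be wider, and it says nothing about deaths before day 7.

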Additionally, multilevel models (generalized linear mixed models) with multivariate logistic link function will be implemented to account for possible correlation between patients admitted to the same medical or surgical units (first level) or hospital (second level).

In case of losses to follow-up, multiple imputation techniques will be used for missing data. In all cases, bilateral contrast will be used and will be considered significant when p<0.05. The analysis will be performed using SPSS v28.

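### The shared Cox predictor list puts nutritional change at discharge into a hospital-mortality model, where no patient who dies can have a value, and leaves the timing of day-7 change undefined

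*Protocol article*

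**What the plan says.** All places are in the protocol article.

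- **Data analysis**, the model: "In the case of mortality and time to readmission, multivariate Cox regression models will be fitted". One list of independent variables follows for both outcomes. Besides malnutrition risk and diagnosis at admission, it contains "change in risk of malnutrition at admission, at 7 days and at discharge" and "change in nutritional status at admission, at 7 days and at discharge". The adjustment set begins: "Control variables will include: type of nutritional care established (according to risk of malnutrition); daily intake".
- **Data analysis**, missing data: "In case of losses to follow-up, multiple imputation techniques will be used for missing data".
- **Aims**, third specific objective: "To analyze the average length of stay, hospital mortality, and early readmission as a function of nutritional status at admission".
- **Phase 3: Situation on discharge**: "The variables related to the care process (days of stay, hospital mortality, and whether it was early readmission) will also be recorded". The Research hypothesis and the Conclusions also speak of hospital mortality.
- **Variables and instruments**, on MUST: "All patients included in the study will be assessed on admission, every 7 days, and at discharge". Under Phase 2, scheduled monitoring stops at discharge.
- **Sample/Participants**: an expected stay of 48 h or more is enough for entry, so stays that end before day 7 are eligible.

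The article does not say whether the change variables are fixed, time-dependent or landmarked. It also does not say from what point the survival clock runs.

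**The concern.** A predictor in a Cox model must be known while the patient is still at risk. For hospital mortality, the patient stops being at risk at death or at live discharge. Change at discharge becomes known only at live discharge, so it is tied to not having the event. Change at day 7 becomes known only to those still in hospital on day 7.

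The Research hypothesis is that nutritional status evolves unfavourably during the stay and may raise hospital mortality, among other outcomes. The Cox model is the only multivariable survival analysis described that links evolution to death. If its evolution terms cannot be estimated, or are coded so that surviving longer gives more chance to be recorded as worsened, that part of the hypothesis goes untested or is answered in the wrong direction.

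**Working it through.** **1. The plan's own figure.** The article gives no event count, hazard ratio or power for the Cox models. The only governing figure is the sample size: 1.96² × 0.5 × 0.5 / 0.05² = 384.15, rounded up to 385; 385 / 0.85 = 452.9, rounded up to 453; 9 × 453 = 4077. It reproduces, and is used here only as the simulation size.

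**2. Discharge change in the hospital-mortality model.** This needs no assumed rates. Hospital deaths with a live-discharge assessment: 0. The possible treatments are:

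- *Complete case:* every death is dropped, no events remain, and there is no hazard ratio.
- *Time-dependent:* the value begins at the moment the patient leaves the risk set, so it contributes no time at risk.
- *Imputed for deaths:* the model would use a status that never existed.
- *Deaths coded as unchanged, or last value carried forward:* longer survival gives more occasions to be recorded as worsened, so worsening tends to look protective.

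None gives a valid hazard ratio for this term.

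**3. Day-7 change.** Assumed, not from the documents: death and discharge compete with constant hazards; mean stay L is 6, 8 or 12 days; hospital mortality is 3, 5 or 10%; 20% would be classed as worsened if measured at day 7, independently of death (true HR 1.0). The 48 h minimum is not modelled.

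Share still in hospital at day 7: p = exp(−7/L). Share of deaths before day 7: 1 − p.

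Suppose that worsening is coded as known from admission and that unmeasured patients count as not worsened. The worsened group is then a fraction q = 0.2p of all patients, each with 7 event-free days by construction and a mean stay of 7 + L. The crude death-rate ratio, in which mortality cancels, is

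[1/(7 + L)] ÷ [(1 − q)/(L − q(7 + L))].

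- L = 6: p = 0.311, q = 0.0623; 0.0769 ÷ (0.9377/5.190) = 0.43
- L = 8: p = 0.417, q = 0.0834; 0.0667 ÷ (0.9166/6.749) = 0.49
- L = 12: p = 0.558, q = 0.1116; 0.0526 ÷ (0.8884/9.879) = 0.59

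Cox fits to simulated data (n = 4077, 30 runs per scenario) agree. The three values in a cell are for mortality 3, 5 and 10%:

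| Mean stay | Reach day 7 | Deaths before day 7 | HR, unmeasured = not worsened | HR, day-7 landmark |
|---|---|---|---|---|
| 6 days | 31% | 68, 69, 69% | 0.46, 0.38, 0.43 | 1.11, 0.91, 1.01 |
| 8 days | 42% | 56, 58, 58% | 0.51, 0.48, 0.45 | 1.01, 0.98, 0.93 |
| 12 days | 56% | 45, 43, 45% | 0.59, 0.57, 0.57 | 1.03, 0.97, 0.98 |

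Restricting to patients with a day-7 value, with the clock from admission, gave the same estimates as the landmark, because nobody in that subset can die before day 7. The scatter around 1.0 is simulation noise. With 3% mortality and a 6-day stay, about 4077 × 0.03 × 0.31 = 38 deaths fall after day 7, of which about 8 are in the worsened fifth.

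**The case against.** **The coding is not stated.** A reader might infer that the change variables are treated as fixed at admission and that the hazard ratios therefore carry immortal-time bias. The article does not say this. Weekly reassessment is compatible with time-dependent coding, and a condensed article may leave coding and time origin to the analysis plan. This stands: for the day-7 term the bias is conditional. For the discharge term immortal-time bias is not the main diagnosis; the term has no value for the events.

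**The size is illustrative.** The 0.4 to 0.6 range needs the unstated rule that unmeasured means not worsened. A larger distortion can be produced: another null simulation, with deterioration of 3% per day, mortality near 3.9% and mean stay 9.7 days, gave about 0.25 with fixed coding and 0.98 with time-dependent coding. That is one assumed scenario under a fixed coding that the article does not state, and should not be read as the expected error.

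**Imputation of deaths is not stated.** Multiple imputation is planned for losses to follow-up, and a death is an outcome rather than a loss. This stands: the article does not say that deaths will be given an imputed discharge status. It also does not rule it out.

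**Adjustment for care and intake.** A reader might infer that controlling for nutritional care and daily intake removes the effect of admission status through its own mediators. Care is recorded within 48 h as well as later, the article does not say which value is used, and the third objective does not specify a total effect. The calculations above do not test this. It justifies at most a sensitivity analysis.

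**One of the two outcomes is unaffected.** Discharge change is a legitimate predictor of readmission if the clock starts at discharge. The main objective is nutritional status and its evolution; mortality belongs to the third specific objective, which refers to admission status.

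None of this rescues discharge change in the mortality model. The article names that predictor for that outcome, describes mortality only as hospital mortality, and mentions no collection of deaths after discharge. An analysis plan could not make the term work without removing it.

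**Conclusion.** The point holds in two parts of different strength.

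- **Discharge change as a predictor of hospital mortality is wrong as written.** No hospital death can carry the value, and no coding yields a valid hazard ratio. This follows from the article's own definitions and rests on no assumed rate.
- **Day-7 change is underdefined.** Under the assumed stays, 31 to 56% of patients reach day 7 and 43 to 69% of hospital deaths come before it, so the choice of coding matters. Counting the unmeasured as not worsened from admission would turn a true hazard ratio of 1.0 into about 0.4 to 0.6, opposite in direction to the hypothesis. A landmark, time-dependent coding or restriction to patients with a day-7 value gave 1.0 within simulation error where tested, or avoids the problem by construction. The documents do not show that the biased coding is intended.

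The readmission model is not at fault on this point, provided time zero is discharge.

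**What to change.** Split the Cox predictor list by outcome.

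1. **Hospital mortality, main model:** MUST and GLIM status at admission, as in the third specific objective.
2. **Hospital mortality, evolution:** enter later change only as a time-dependent covariate that counts from its measurement date, or in a day-7 landmark analysis of patients still in hospital.
3. **Remove discharge change from the mortality model**, and state that discharge status is not imputed for patients who die.
4. **Readmission:** keep discharge change here only, among live discharges, with time zero at discharge. This assumes that readmission dates are available, as the planned time-to-readmission model implies.
5. **Optional sensitivity analysis:** refit the admission-status model without nutritional care and intake recorded after admission.

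The cost is a change of wording and minor restructuring of the data into start-stop records. Weekly assessments, and start dates when care is modified, are already to be collected. The sample size of 4077 is unchanged.

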## Introduction

Malnutrition is a recurring problem that has become more relevant in recent years and people aged 65 years and older are common at all levels of health care. Moreover, malnutrition can be aggravated by the presence of diseases and problems such as dysphagia [1]. In particular, assessment and monitoring of nutritional status and dysphagia during hospitalization processes are crucial to provide the highest quality care to avoid undesirable outcomes such as susceptibility to infection, morbidity, and mortality and increased premature readmissions, as well as longer length of stay [2].

Malnutrition is the result of a deficit in the intake or assimilation of nutrients that alters body composition, leading to a decrease in physical and mental capacities, which hinders recovery during an illness process [3]. In Europe, this problem affects approximately 30 million people and costs approximately 170 billion euros per year [4]. Disease-related undernutrition, on the other hand, is caused by inadequate nutrient and energy intake about nutritional requirements in a situation where disability and disease are at the core of the problem. This type of malnutrition is due to the bodily changes and loss of functionality that occur when there is an acute or chronic illness [5]. Furthermore, different studies show that the nutritional status of patients worsens during hospitalization [1], increasing morbidity and mortality, hospital stay, and costs for the healthcare system [6,7].

People aged 65 years and older are particularly susceptible to undernutrition and disease-related undernutrition. This is due to physiological changes during ageing, the presence of associated diseases, and the specific nutritional needs of this population (decreased activity, alterations associated with swallowing disorders or frailty, among others) [8,9]. In this regard, international studies estimate that between 35–65% of older people in hospital settings are undernourished [10,11].

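### Objective 3 makes dysphagia an exposure for mortality and readmission, but the Cox models carry it only as a control beside post-admission nutrition variables

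*Protocol article*

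**What the plan says.** The third specific objective in the Aims section reads "To analyze the average length of stay, hospital mortality, and early readmission", to be studied "as a function of nutritional status at admission and the presence of dysphagia in the study cohort". Nutritional status and dysphagia stand side by side there as exposures. The Variables and instruments section gives them equal rank: "nutritional status and dysphagia are considered the main variables of the study".

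For two of the three outcomes the Data analysis section names the model: "In the case of mortality and time to readmission, multivariate Cox regression models will be fitted". It then assigns roles. The exposures begin "Independent variables will be included: level of risk of malnutrition at admission; diagnosis of malnutrition at admission" and continue with change in risk and change in nutritional status up to 7 days and discharge. All are nutritional. The controls include nutritional care, daily intake, context and risk profile, and end with "sociodemographic; clinical, functional, cognitive and frailty variables; suspected and diagnosed dysphagia".

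On how these variables relate, the Introduction says that "malnutrition can be aggravated by the presence of diseases and problems such as dysphagia". The Phase 1 and Phase 2 sections say that nutritional care is adapted after a positive dysphagia screen, and again during the stay according to the degree of dysphagia.

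**The concern.** Dysphagia as a control is reasonable when the exposure is malnutrition. The difficulty comes when the dysphagia coefficient of the same model is used for the other half of objective 3. That coefficient compares patients with and without dysphagia who have the same intake, the same nutritional care and the same nutritional course in hospital. If dysphagia changes any of these, part of its association with death or readmission has been conditioned away or distorted.

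At stake is what the study can say about one of its two main variables. As specified, it would have either an unadjusted comparison from the bivariate step, open to confounding by age, frailty and comorbidity, or a coefficient conditional on events after admission. Neither is mortality or readmission as a function of dysphagia, adjusted for the patient's state at admission.

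**Working it through.** **Plan's own figure.** The only calculation in the article is the sample size. With z = 1.96, 1.96² × 0.5 × 0.5 / 0.05² = 384.1, rounded up to 385; 385 / 0.85 = 453 per hospital; 453 × 9 = 4077. It reproduces, but it concerns the precision of a prevalence and does not bear on this point.

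**Is there another model for dysphagia and these outcomes?**
- The logistic models that list dysphagia as an independent variable have malnutrition and dysphagia as outcomes.
- The multilevel models have a logistic link and name neither exposure nor outcome.
- The bivariate step names no groups and is unadjusted.

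So no specified multivariable model has dysphagia as the exposure for mortality or readmission.

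**When do the other covariates arise?**
- Daily intake is recorded through the stay: after admission.
- Nutritional care is recorded within 48 hours, every 7 days and at discharge, and is adapted to dysphagia: after admission and partly a consequence.
- Change in risk and nutritional status to 7 days and discharge: after admission.
- Malnutrition risk and diagnosis at admission are collected in the same 24–48 hour window as the dysphagia instruments. The order is unknown, so this may be confounder or mediator.

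**How far could the two hazard ratios (HR) differ?** The article gives no hazard ratios or event rates, so every input here is an assumption: direct dysphagia HR 1.3; malnutrition in 50% with and 27% without dysphagia; malnutrition HR 2.0 or 1.5. With dysphagia at 44% (the Introduction's upper figure for older inpatients), overall malnutrition is 0.44 × 0.50 + 0.56 × 0.27 = 37%, the Introduction's figure for patients over 70. For rare events:

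overall HR ≈ 1.3 × [1 + 0.50(h − 1)] / [1 + 0.27(h − 1)], where h is the malnutrition HR.

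- h = 2.0: 1.3 × 1.50 / 1.27 = 1.535
- h = 1.5: 1.3 × 1.25 / 1.135 = 1.432

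Now let nutritional care reach 70% with and 30% without dysphagia, with a protective HR of 0.7, acting independently of malnutrition given dysphagia. The multiplier is (1 − 0.70 × 0.3) / (1 − 0.30 × 0.3) = 0.79 / 0.91 = 0.868.

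- h = 2.0: 1.535 × 0.868 = 1.33
- h = 1.5: 1.432 × 0.868 = 1.24

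| Malnutrition HR | Protective care | Overall HR | Conditional HR | Log HR removed |
|---|---|---|---|---|
| 2.0 | no | 1.54 | 1.30 | 1 − 0.262/0.429 = 39% |
| 1.5 | no | 1.43 | 1.30 | 1 − 0.262/0.359 = 27% |
| 2.0 | yes | 1.33 | 1.30 | 1 − 0.262/0.287 = 9% |
| 1.5 | yes | 1.24 | 1.30 | 1 − 0.262/0.217 = −21% |

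The last row is negative: the conditional estimate is then the larger of the two.

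**Simulation check of the malnutrition pathway alone.** Cox fits on 100,000 simulated patients per scenario assumed dysphagia 30%, malnutrition 25% without dysphagia, odds ratio of dysphagia for malnutrition 2 to 4, malnutrition HR 1.5 to 2.5 and direct HR 1.3. Overall HRs were 1.38 to 1.81 and conditional HRs 1.26 to 1.33, a removal of 19% to 52% of the log HR. With a direct HR of 1.0 and odds ratio 3, overall HRs of 1.11 to 1.26 appeared as about 1.0. These runs treat malnutrition purely as a mediator and do not model intake, care or later change.

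**The case against.** **Dysphagia is in the model anyway.** The labels independent and control make no difference to the fit, so an adjusted dysphagia hazard ratio will be produced. Objective 3 is worded as an association and promises no total causal effect, and the hypothesis and main objective concern nutrition. This is fair, but the covariates decide what the coefficient means, and holding in-hospital intake, care and nutritional change fixed does not give the association stated in the objective.

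**The covariates may not all enter together.** The article speaks of models in the plural, and its sample size section allows at most 20 independent variables at once in the logistic model. An article may also leave adjustment sets to a fuller document. This stands in part: the exact fits are unknown. But the article did assign roles, and in that assignment dysphagia is never the exposure for these outcomes.

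**Admission malnutrition may be a confounder.** This stands. It is measured alongside dysphagia, and leaving it out could introduce confounding. The clear case is confined to the post-admission variables.

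**The care covariate is tied to malnutrition risk.** Care for dysphagia is recorded separately. That weakens the link, but Phases 1 and 2 state that nutritional care is itself adapted to dysphagia.

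**Stronger readings.** A reader might infer that the coefficient is biased toward no effect, that adjusting for intake and care can only remove more, or that the study loses a calculable amount of power. The documents support none of these. Protective care can move the estimate the other way, as the last row of the table shows. Power for the overall and for the conditional association concerns two different quantities, each on assumed inputs.

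**Conclusion.** The mismatch is real and stands in the text: objective 3 has two exposures, and the models for mortality and readmission serve one. The dysphagia hazard ratio they yield is conditional on nutrition, partly a direct association, and does not answer the objective.

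The size cannot be fixed from the documents. Under the assumed inputs above, conditioning removes anywhere from 52% of the log hazard ratio to less than nothing (−21%). These figures show only that the two quantities can differ materially in either direction. The conclusion itself rests on the assigned variable roles, the timing of measurement, and the article's own statements that dysphagia can worsen malnutrition and that care is adapted to it.

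The planned analysis of the malnutrition exposures is not called into question by this point. The change should be made, since it is cheap and otherwise half of a numbered objective has no suitable adjusted estimate.

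**What to change.** In the Data analysis section:

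1. Name dysphagia at admission as an independent variable for objective 3.
2. Fit one further model each for mortality and readmission with that exposure, adjusted only for sociodemographic, comorbidity, functional, cognitive, frailty, risk-profile and context variables measured at admission.
3. Leave daily intake, nutritional care and post-admission change in risk or nutritional status out of these models.
4. Report the dysphagia estimate both with and without admission malnutrition, since that variable may be confounder or mediator.
5. Keep the existing models for the malnutrition exposures, and label their dysphagia coefficient as conditional on nutrition.

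The cost is a change of wording and additional fits on data already collected. Recruitment, measurements and care are unaffected. The downside is one more set of estimates to report.
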